**Genotyping**

It is estimated that 2-year toxicity data (1-year for lung) will be available for 75% of enrolled patients. Based on effect sizes observed for genetic associations with radiation toxicity, a power calculation for the genetic assays shows that 1,575 patients for breast and prostate cancer each has 80% power to detect a RR of >1.56 for at least grade 2 toxicity (α = 5 x 10^-5^ for 1000 SNPs, allele freq = 0.25, toxicity rate = 20%), or with more stringent criteria a 90% power to detect a RR >1.66 (α = 1 x 10^-5^, allele freq = 0.25, toxicity rate = 20%). For 825 patients with lung cancer the detectable RR would be 1.78 and 1.92.

## 7.2 Statistical Data Analysis

In a first stage the data from the REQUITE multi-centre observational study will be used to validate published statistical models that use clinical and biomarker data to predict a patient’s risk of long-term side-effects following radiotherapy in patients with prostate, breast or lung cancer. Variables considered will be dose-volume data of organs and tissues at risk, dose fractions and overall treatment time, patient-related cofactors (e.g. age, weight, diabetes, and smoking), use of concurrent treatment (e.g. chemotherapy) and genotyping data. If necessary, individual clinical toxicity endpoints will be combined to derive tissue, organ or overall radiosensitivity measures (e.g. by STAT score or principal component analysis). Validation of risk factors will involve univariate analysis with Bonferroni correction and multivariate analysis. The strength of association of predictors will be assessed by calculation of the odds ratios.

Nomograms, logistic regression-, ordinal logistic regression-, and NTCP (normal tissue complication probability) models published in the literature will be considered for the prediction model validation. Validation of the prediction models in the REQUITE cohort will be evaluated by: (a) Calibration: assessing the agreement between observed and predicted probabilities using the Hosmer-Lemeshow “goodness-of-fit” test. (b) Discrimination: assessing the ability of the models to discriminate between those with and those without toxicity. For binary endpoints the area under the receiver operating curve (ROC) will be used with derivation of sensitivity and specificity for a chosen probability threshold. For polychotomous endpoints c-statistic will be used as rank order statistic. (c) Clinical usefulness: the “net benefit” (NB) will be calculated (NB=(TP−wFP)/N, where TP is the number of true-positive classifications, FP the number of false-positive classifications). w is a weight equal to the “ratio of harm to benefit” (w=cutoff/(1−cutoff), where cutoff is the probability threshold which is chosen to define the treatment rule (e.g.: the level of non-acceptable toxicity)). A clinically useful model should have an NB>cut-off.

In a second stage existing models will be improved and extended using the biomarker data (SNPs, apoptosis data) in large cohorts recruited via the REQUITE study. Derivation of these models will involve separating cohorts into discovery and validation cohorts. The following performance measures will be considered for improvement and extension of existing models: (a) Likelihood-ratio test: comparing the fits of two models, the null model versus the alternative model. (b) Reclassification table (i.e. percent of individuals who change risk category when applying an advanced model). (c) Net Reclassification Improvement (NRI; i.e. for patients with toxicity any upward shift in risk classes implies prediction improvement and any downward shift indicates reduced reclassification. The reverse holds for patients without toxicity.

In both stages appropriate statistical methods are used as described in the statistical operating procedure (SOP) for statistical analysis.

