# 5.0 RECRUITMENT OF PATIENTS

## 5.1 Number of patients required

A total of 5,300 patients are to be recruited. Approximate breakdown: 2,100 breast patients; 2,100 prostate patients and 1,100 lung patients.

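### Section 7.2 names only the Hosmer-Lemeshow test for calibration of published models, which gives neither size nor direction of miscalibration and depends strongly on cohort size

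*Protocol*

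**What the plan says.** Section 7.2 of the Protocol sets out a first stage in which existing models are tested in the REQUITE cohort. The candidates are "Nomograms, logistic regression-, ordinal logistic regression-, and NTCP (normal tissue complication probability) models published in the literature". Their predictions are therefore fixed before the REQUITE outcomes are seen, so this is external validation.

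Performance is to be evaluated under three heads:
- **Calibration.** "Calibration: assessing the agreement between observed and predicted probabilities using the Hosmer-Lemeshow" goodness-of-fit test. No intercept, slope, plot, significance level, number of groups, degrees of freedom or acceptance rule is given.
- **Discrimination.** Area under the ROC curve, or the c-statistic for endpoints with more than two categories.
- **Clinical usefulness.** "Clinical usefulness: the “net benefit” (NB) will be calculated" at a chosen probability threshold.

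The section closes with a general reference: "In both stages appropriate statistical methods are used as described in the statistical operating procedure (SOP) for statistical analysis". That procedure is not shown.

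Cohort sizes come from two places. Section 5.1 plans "2,100 breast patients; 2,100 prostate patients and 1,100 lung patients". Section 7.1 (Genotyping) expects that "2-year toxicity data (1-year for lung) will be available for 75% of enrolled patients", and works with 1,575 patients each for breast and prostate and 825 for lung.

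**The concern.** The first stage has to tell the sponsor whether a published model can be used as it stands, needs recalibration, or should be set aside. That requires three facts about calibration: whether the average predicted risk is too high or too low, by how much, and whether the spread of predicted risks is too wide or too narrow. A Hosmer-Lemeshow p-value supplies none of them.

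The other two heads do not fill the gap. The area under the curve and the c-statistic measure ranking and do not change when every prediction is inflated. Net benefit reacts to miscalibration at the chosen threshold but does not measure it.

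The p-value also mixes the size of the error with the size of the cohort. For a fixed error, the non-centrality of the statistic grows in proportion to n. The lung cohort is about half the size of the other two, so a non-significant result there carries much less reassurance than the same result in breast or prostate. Nothing in the output shows this to the reader.

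**Working it through.** **1. The Protocol's cohort sizes reproduce.** Breast and prostate: 0.75 × 2,100 = 1,575 each. Lung: 0.75 × 1,100 = 825. These match "1,575 patients for breast and prostate cancer each has 80% power" and "For 825 patients with lung cancer the detectable RR would be 1.78 and 1.92". At the 20% toxicity rate assumed in section 7.1, that is 0.20 × 1,575 = 315 events and 0.20 × 825 = 165 events. The 400 lung samples planned for the apoptosis assay (section 7.1, Live Cell Assays) would hold 0.20 × 400 = 80 events.

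**2. Set-up.** From the Protocol: a 20% event rate and the cohort sizes. Assumed, because the Protocol does not give them: 10 risk groups, a 5% level, and a normal linear predictor with SD 0.5 or 0.8 on the logit scale (area under the curve 0.64 or 0.70 when calibrated). The statistic is the sum over groups of (O − E)² / [n·p̄(1 − p̄)], where O and E are observed and expected events, and n and p̄ are the group's size and mean predicted risk. For predictions fixed in advance it is referred to chi-square with 10 df (critical value 18.31). Rates come from 3,000 simulated cohorts per cell.

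**3. Rejection rates, 10 df.** Ranges cover the two SDs.

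| Model | n = 400 | n = 825 | n = 1,575 |
|---|---|---|---|
| Correctly calibrated | 5% | 5% | 5–6% |
| Predicts 25%, 20% occur | 19–21% | 56–58% | 93–94% |
| Slope 0.7, average right | 11–22% | 18–40% | 29–67% |
| Slope 0.5, average right | 25–54% | 43–85% | 75–99% |

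The 25% versus 20% error is a shift of 0.30 logit (SD 0.5) or 0.32 logit (SD 0.8). Applying 0.30 at both SDs gives slightly lower rates in a separate run: 18–20%, 53–55% and 89–92%. The slope rows depend heavily on the assumed spread. The over-prediction row does not.

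**4. Small errors at n = 1,575.**
- Slope 0.9: rejected 7–11%.
- 21.5–21.6% predicted against 20%: 10–11%.
- 22% against 20%: 15–18%.
- 23% against 20%: 42–47%.

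**5. Degrees of freedom.** With 10 groups, 8 df is the convention for a model fitted to the same data (critical value 15.51). For fixed predictions, P(chi-square with 10 df > 15.51) = 0.115. A perfectly calibrated published model would be rejected about 11% of the time instead of 5%, at every n.

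**6. What an estimate would show.** The 95% half-width for the intercept is 1.96/√(n·w), where w is the mean of p(1 − p): about 0.154 at SD 0.5 and 0.145 at SD 0.8. For example, 1.96/√(825 × 0.154) = 0.174. Slope half-widths come from the inverse information matrix.

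| n | Intercept (logit) | Slope (SD 0.5 / 0.8) |
|---|---|---|
| 400 | ±0.25–0.26 | ±0.52 / 0.35 |
| 825 | ±0.17–0.18 | ±0.36 / 0.25 |
| 1,575 | ±0.13 | ±0.26 / 0.18 |

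The estimand is the same at every n. Only the visible precision changes.

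**The case against.** **The detail may sit elsewhere.** Section 7.2 does not say the Hosmer-Lemeshow test is the sole criterion, and it refers to an operating procedure that may add measures. This stands. A reader might infer that calibration will be judged by this test alone, or that a non-significant result will be taken as agreement. The text states neither. What remains is that the Protocol names a specific tool for the task, and that tool does not deliver the quantity needed.

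**Large cohorts.** A reader might also infer that nearly correct models will be thrown out at n = 1,575. Step 4 does not support that. Truly small errors are rejected about 7% to 18% of the time, against 5% for a perfect model. Even 23% versus 20% passes more often than it fails.

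**Small subsets.** The apoptosis samples are not clearly part of this analysis. The first-stage variable list includes genotyping but not apoptosis. Apoptosis data are named in the second stage, whose listed measures are the likelihood-ratio test, the reclassification table and net reclassification improvement. The 400-patient column is therefore conditional. The smallest cohort clearly tied to the test is lung, at 825. Gross errors are also caught fairly often even at 400: 28–29% against 20% is rejected 71–74% of the time.

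**Degrees of freedom.** The Protocol states none, so step 5 is a caution and not an error in the text.

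**Intervals can be misused in the same way.** If a model were flagged whenever the interval for intercept or slope excluded its ideal value, a 3-point over-prediction would be flagged in 60% of cohorts at 825 and 86% at 1,575. That rule also depends on n. The objection is right, and it shapes the fix.

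**No cross-cancer comparison is planned.** The primary endpoints differ by tumour. This also stands. The contrast between 825 and 1,575 shows how much the verdict on any one model owes to cohort size. It does not show that one model will receive two verdicts.

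**Conclusion.** The point holds as a worthwhile improvement to a method the Protocol names. It is not a flaw that invalidates the analysis. For external validation of published models, the only calibration tool in section 7.2 gives no size or direction of error. Its verdict on a 5-point over-prediction goes from about 55% rejection in lung to over 90% in breast or prostate, and would be about 20% in a 400-patient subset if the test were run there.

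These figures rest on 20% events (from section 7.1) and on assumed values for the number of groups, the significance level and the spread of predicted risks. The over-prediction result is stable over the two spreads tried, while the slope results vary widely. The documents do not support reading this as wholesale rejection of good models in the large cohorts, or as proof that no other calibration measure will be used.

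**What to change.** In section 7.2, under calibration:

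- For each published model, make calibration-in-the-large (the intercept) and the calibration slope, each with a 95% confidence interval, together with a smoothed calibration plot, the calibration measures.
- State that models are judged by the size of these estimates, with the intervals showing their uncertainty, and not by whether an interval excludes the ideal value of 0 or 1.
- Keep the Hosmer-Lemeshow test as supplementary only. Where predictions are fixed in advance, set the degrees of freedom equal to the number of groups (10 for 10 groups).

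The operating procedure for statistical analysis should carry the same wording. No extra patients, data or visits are needed, only a few sentences and standard output. The one thing to accept is that the lung intervals will be visibly wide (about ±0.17 to 0.18 logit for the intercept and ±0.25 to 0.36 for the slope). That is information a p-value would have hidden.

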## 2.2 Long-term side-effects of radiotherapy impact on quality-of-life

Radiotherapy represents the most effective non-surgical modality in the curative treatment of cancer. Around a half of all cancer patients receive radiotherapy at some point in their treatment and nearly a half of all cancer survivors underwent radiotherapy as part of their care^[[3]](#footnote-3)^.

Yet, many patients receiving potentially curative radiotherapy will experience toxicity due to the unavoidable irradiation of surrounding healthy tissue. The toxicity varies in severity from minor to severe and in duration from weeks to a lifetime. Around 3-5% of people suffer with severe long-term side-effects but more experience moderate toxicity such as poor breast cosmetic outcome, incontinence, erectile dysfunction, chronic breathlessness, and chronic pain. Moderate toxicity, such as a poor cosmetic outcome following breast cancer treatment, can have a marked effect on subsequent psychological outcome^[[4]](#footnote-4)^. The long-term side-effects of radiotherapy have been shown to impair quality-of-life in cancer survivors^[[5]](#footnote-5),^^[[6]](#footnote-6),^^[[7]](#footnote-7)^. The ability to predict those patients likely to develop toxicity could potentially enable individual dose prescription to be made, which should improve survival and decrease morbidity.

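### The clinical-usefulness rule compares net benefit with the risk threshold instead of with the classify-all and classify-none strategies, and gives wrong verdicts in both directions

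*Protocol*

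**What the plan says.** Protocol section 7.2 lists three criteria for validating published prediction models in the REQUITE cohort: calibration, discrimination and clinical usefulness. For the third it gives the formula "NB=(TP−wFP)/N, where TP is the number of true-positive classifications, FP the number of false-positive classifications". The weight w is the odds of the cut-off, c/(1 − c), and the cut-off is explained by the words "where cutoff is the probability threshold which is chosen to define the treatment rule". The section then sets its benchmark: "A clinically useful model should have an NB>cut-off".

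It names no comparison strategy. It closes with a general reference to a statistical operating procedure, which is not part of the document.

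**The concern.** The formula and the weight are the standard ones; the benchmark is not. NB is expressed in net true positives per patient. The cut-off is a risk, and it has already entered NB through the weight. Using it again as the pass mark has no decision-analytic meaning.

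A model has clinical value at a threshold if acting on it does better than the two strategies that need no model: calling no one high risk, or calling everyone high risk. The stated rule tests neither.

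Sections 2.3 and 2.4 give model validation, ahead of interventional trials, as the reason for the study. A wrong verdict on usefulness could discard a model worth taking forward, or endorse one that does no better than treating all patients alike.

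**Working it through.** The protocol states a rule here, not a figure, so there is no number to reproduce. The check applies the protocol's own formula.

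**Inputs**
- NB formula, weight and meaning of the cut-off c: section 7.2.
- Event rate p = 0.20: the toxicity rate in the power calculations of section 7.1, where the genotyping paragraph refers to at least grade 2 toxicity.
- Evaluable patients: 1,575 each for breast and prostate (section 7.1), so 0.20 × 1,575 = 315 events.
- Lower event rate for sensitivity: "Around 3-5% of people suffer with severe long-term side-effects" (section 2.2).
- AUC values: **assumed**, because the protocol gives none.

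**Formula.** Per patient, NB = p × sens − (1 − p) × (1 − spec) × c/(1 − c).

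**Step 1: the ceiling.** A perfect model has sens = spec = 1, so NB = p. At p = 0.20 this is 315/1,575 = 0.20. The rule NB > c therefore cannot be met by any model once c ≥ 0.20. At p = 0.05 it cannot be met once c ≥ 0.05.

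**Step 2: classify everyone as high risk.** With sens = 1 and spec = 0, NB = p − (1 − p)c/(1 − c) = (p − c)/(1 − c). This exceeds c when c² − 2c + p > 0, that is, when c < 1 − sqrt(1 − p).
- At p = 0.20 the limit is 1 − sqrt(0.8) = 0.1056.
- At c = 0.05, NB = 0.15/0.95 = 0.158, which passes.
- At c = 0.10, NB = 0.10/0.90 = 0.111, which passes.

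**Step 3: a coin flip.** With sens = spec = 0.5 and c = 0.05, NB = 0.20 × 0.5 − 0.80 × 0.5 × 0.05/0.95 = 0.100 − 0.021 = 0.079. This passes the rule (0.079 > 0.05), although it is half the 0.158 obtained by classifying everyone.

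**Step 4: other event rates**

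| Event rate p | Classify-all passes below c = | Even a perfect model fails from c = |
|---|---|---|
| 5% | 0.025 | 0.05 |
| 10% | 0.051 | 0.10 |
| 20% | 0.106 | 0.20 |
| 30% | 0.163 | 0.30 |

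**Step 5: realistic models (assumed AUCs), p = 0.20.** These use a calibrated equal-variance binormal model, with d = sqrt(2) × Φ⁻¹(AUC), x = [logit(c) − logit(p) + d²/2]/d, sens = 1 − Φ(x − d) and spec = Φ(x). The correct benchmark is the larger of 0 and the classify-all NB.

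| c (the rule's pass mark) | Classify-all NB | Correct benchmark | NB, AUC 0.70 | NB, AUC 0.80 | NB, AUC 0.90 | Verdict of the rule |
|---|---|---|---|---|---|---|
| 0.10 | 0.111 | 0.111 | 0.118 | 0.132 | 0.154 | all pass, as does classify-all |
| 0.15 | 0.059 | 0.059 | 0.084 | 0.109 | 0.139 | all fail |
| 0.20 | 0.000 | 0 | 0.058 | 0.090 | 0.127 | all fail |
| 0.30 | −0.143 | 0 | 0.026 | 0.061 | 0.107 | all fail |

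Every model in the table beats the correct benchmark at every cut-off shown. To pass the rule, a model of this form needs an AUC of about 0.79 at c = 0.12, 0.93 at c = 0.15 and 0.99 at c = 0.18. A calibrated logistic-normal simulation agrees with the binormal results within 0.002 for AUC 0.70. In that simulation AUC 0.83 gives NB 0.118 at c = 0.15, which also fails.

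**The case against.** The case on the other side concerns weight and framing rather than the algebra.

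- **Scope.** The primary objective is to build a cohort, and the secondary objective is a database and sample resource. The sentence governs one of three stage-one criteria. Calibration, discrimination, the stage-two measures, the endpoints and the sample size do not depend on it. NB can be recomputed later from the same data. All of this is true. It limits the damage but does not make the sentence right.
- **Softness.** The wording is advisory, no consequence is attached to failing, and methods are also referred to an operating procedure that is not shown. But this is the only benchmark the protocol gives for clinical usefulness. A separate procedure would either repeat the error or contradict the protocol, and section 8.1 commits the study to following the protocol.
- **Another reading.** Cut-off might mean a separate NB threshold. The preceding sentence defines it as the probability threshold, and no other is given.
- **Conditional numbers.** This objection stands. The protocol fixes no cut-off, so which failure occurs depends on the one chosen. The 20% rate is a planning input; the breast primary endpoint is any change in appearance, and its rate is not stated. The AUCs are assumptions. For these reasons the limits are shown over a range of event rates and the model examples are labelled as illustrations.

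**Conclusion.** The rule is wrong as written. Two failures follow from the protocol's formula with no assumption about model performance: nothing can pass once the cut-off reaches the event rate, and classifying everyone passes whenever the cut-off is below 1 − sqrt(1 − event rate). At a 20% event rate these limits are 20% and 10.6%. For event rates between 5% and 30% the first moves from 5% to 30% and the second from 2.5% to 16.3%.

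Between the two limits the rule demands discrimination unrelated to whether the model helps; the size of that demand rests on the assumed binormal form. The error is confined to the clinical-usefulness criterion of section 7.2, but it can reverse that verdict either way.

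**What to change.** Replace the benchmark sentence in section 7.2 with wording such as: *A model is considered clinically useful at a given cut-off if its NB at that cut-off exceeds both the NB of classifying all patients as high risk, p − (1 − p)w with p the observed event rate, and the NB of classifying none, which is zero.* Make the same change in the statistical operating procedure if it repeats the rule.

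That sentence is all the error requires. Two additions would be worthwhile but are optional: showing NB over a pre-stated range of cut-offs with bootstrap confidence intervals, and reporting the NB difference between extended and existing models in stage two.

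The cost is one sentence and a trivial extra calculation. Patients, data collection and sample size are unaffected. The change should be made before any model validation is reported.

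### Stage 2 lists the raw percentage of patients who change risk category as a performance measure; it ignores toxicity and cannot show that biomarkers improve a model

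*Protocol*

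**What the plan says.** Section 7.2 of the Protocol has two stages. Stage 1 validates published models by calibration, discrimination and net benefit. Stage 2 goes further: "In a second stage existing models will be improved and extended using the biomarker data (SNPs, apoptosis data"), with this safeguard: "Derivation of these models will involve separating cohorts into discovery and validation cohorts".

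The stage 2 list opens: "The following performance measures will be considered for improvement and extension of existing models". Three items follow.

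- (a) A likelihood-ratio test, which sets a null model against an alternative one.
- (b) A table of movement between risk classes: "Reclassification table (i.e. percent of individuals who change risk category when applying an advanced model").
- (c) The NRI, under which "for patients with toxicity any upward shift in risk classes implies prediction improvement and any downward shift indicates reduced reclassification", with the reverse for patients without toxicity.

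The discrimination and net-benefit measures of stage 1 are not repeated in this list. The text does not say whether the existing model is refitted in REQUITE before the comparison or used with its published coefficients. Further method detail is referred to a statistical SOP that is not shown.

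**The concern.** Item (b) is introduced as a performance measure and defined by the protocol itself as a simple percentage. A percentage of patients moved says how far two models differ. It does not say which is closer to the truth. Any change to a model moves some patients across a cut-off, and that includes adding a marker with no relation to toxicity.

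Stage 2 is where the study judges whether SNPs and the apoptosis assay add to clinical prediction. A reported 15% or 20% reclassified is easily read as a gain, although useless markers can produce the same figure. Because the protocol fixes the definition, an SOP written to follow it would inherit the problem.

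**Working it through.** The protocol states no figure for this measure, so there is none to reproduce.

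**Inputs from the Protocol.** Enrolment is 2,100 breast, 2,100 prostate and 1,100 lung patients (section 5.1). Toxicity data are expected for 75%, with a toxicity rate of 20% and an allele frequency of 0.25 (section 7.1). Evaluable numbers are 0.75 × 2,100 = 1,575 and 0.75 × 1,100 = 825, as the protocol states.

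**Step 1: the outcome is not used.** At N=1,575 and 20% toxicity there are 315 patients with toxicity and 1,260 without. NRI = (up − down)/315 among those with toxicity + (down − up)/1,260 among those without. Take two invented sets of moves:

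| | Toxicity: up / down | No toxicity: up / down | Percent reclassified | NRI |
|---|---|---|---|---|
| Set A | 60 / 20 | 80 / 220 | 380/1,575 = 24.1% | 40/315 + 140/1,260 = +0.238 |
| Set B | 20 / 60 | 220 / 80 | 380/1,575 = 24.1% | −40/315 − 140/1,260 = −0.238 |

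Item (b) gives both the same score, although one model is clearly better and the other clearly worse. This step needs no assumption about cut-offs, split or discrimination.

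**Step 2: size under pure noise.** Assumptions not in the protocol: one clinical score with AUC about 0.67 to 0.68, a 50:50 discovery/validation split, and the cut-offs shown. SNPs have no effect. Both the clinical model and the extended model are fitted in the discovery half; percent reclassified is read in the validation half.

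With ten null SNPs, 12% (cut-off 20%) or 21% (cut-offs 10% and 20%) change category at N=1,575. At N=825 the figures are 16%, or 28% to 29% depending on the run. A second set of runs varied the number of SNPs and used cut-offs of 20% or of 10%, 20% and 30%:

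| N | Cut-offs | Null SNPs | Percent reclassified | Mean validation NRI |
|---|---|---|---|---|
| 1,575 | 20% | 1 | 4% | −0.003 |
| 1,575 | 20% | 10 | 13% | −0.021 |
| 1,575 | 20% | 20 | 18% | −0.042 |
| 1,575 | 10/20/30% | 10 | 29% | −0.019 |
| 825 | 20% | 10 | 17% | −0.037 |
| 825 | 10/20/30% | 10 | 38% | −0.031 |

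So (b) rises as more useless markers are added, and it does so in the validation half. AUC fell on average in every row.

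**Step 3: items (a) and (c) with a refitted comparator.** In the same runs the likelihood-ratio test at 5% rejected in 3% to 8% of runs (3% to 7% at N=1,575), close to its nominal level. Mean validation NRI was zero or negative. Read in the discovery half instead, mean NRI was positive (+0.003 to +0.257), so the validation cohort is the place to read it.

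**Step 4: items (a) and (c) if the published model were frozen.** No biomarker is added here, N=1,575, and the existing model is only recalibrated. If it predicts 10%, 30% or 40% on average against a true 20%, validation NRI is +0.08 to +0.18 with AUC change 0.000. If only its slope is wrong, NRI ranges from −0.15 to +0.22. In a separate setting, with ten null SNPs added and cut-offs of 10% and 20%, a published model predicting 15% gave a positive NRI in only 14% of runs. A frozen comparator would therefore distort the result, but the sign depends on the kind of miscalibration and on the cut-offs.

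**The case against.** The strongest reply is that (b) is not read alone. Item (c) follows directly and scores the same movements by toxicity status, so (b) gives the amount of movement and (c) its direction. No threshold or decision rule is attached to (b). Markers are to be chosen for strong published evidence (section 6.6.1), so forcing in ten null SNPs is harsher than the plan. Cut-offs, split and comparator are details that an SOP commonly holds.

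Much of this stands. A reader might infer that stage 2 as a whole rewards useless biomarkers, or that one measure can never fail. The text does not support either reading: (a) and (c) use the outcome, a validation cohort is planned, and there is no pass rule to fail.

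A reader might also infer that the likelihood-ratio test and the NRI will credit biomarkers with what is only local recalibration. That needs published coefficients to be held fixed. The protocol never says so, and a likelihood-ratio test ordinarily compares nested models fitted to the same data. Even with a frozen model the shift can go against the biomarkers.

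What does not stand is that the company of (c) makes (b) a measure of improvement. The protocol calls it a performance measure and defines it without the outcome. Careful marker selection may reduce the noise component, but it does not let the percentage separate gain from harm. A single null SNP already moved 4% of validation patients at N=1,575 with a 20% cut-off.

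**Conclusion.** The point holds for item (b). As defined, it cannot tell a better model from a worse one, and Step 1 shows this by counting alone. The noise figures illustrate its size under the assumed AUC, split, cut-offs and number of null SNPs. Other choices would change the size, but the measure would stay blind to outcome.

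For (a) and (c) there is no error in what is written, only an unnamed comparator worth clarifying. With the clinical model refitted in the same data, and the NRI read in the validation cohort, neither rewards useless markers beyond chance.

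**What to change.** In the stage 2 part of section 7.2:

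1. Delete the percentage reclassified as a performance measure. Alternatively, show the reclassification table only split by observed toxicity, with the observed toxicity rate in each cell.
2. Carry the stage 1 discrimination and net-benefit measures into stage 2, reported as changes between the two models in the validation cohort with confidence intervals.
3. As a clarification, state that the comparator is the clinical-only model re-estimated in the same discovery cohort.

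The cost is a few sentences in section 7.2 and the statistical SOP, plus one extra fit of the clinical-only model per endpoint where it is not already planned. No new data are needed. The downside is a little more analysis, and reported biomarker gains may look smaller.
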